#### Inhibition training: go/no-go

The goal of is to systematically learn to suppress a response towards unhealthy food stimuli. The training manipulation is based on a 90/10 contingency relationship between the letters and the stimuli. For the experimental group, there is a connection between the cue (no/go) and the nature of the picture (healthy/neutral). In 90% of the cases, the no-go cue is paired with an unhealthy picture, expected to lead to more inhibition towards unhealthy food [43]. In the sham-training of the active control group, the only difference is a 50/50 contingency relationship between the cues and the stimuli [32].

#### Attention training: dot probe

The goal of this task is to transform an attention bias towards unhealthy food into a bias away from unhealthy food. Again, in the training manipulation, there exists a 90/10 a contingency relationship between the location of the dot (left-right) and the nature of the picture (unhealthy/neutral). In 90% of the trials, the dot appears on the location of the cue with a neutral photo, to direct attention away from unhealthy food. For the sham-training in the active control group, the only difference is the equal 50/50 proportion in dots paired with unhealthy and with neutral photos [68].

#### Drop-out, motivation and feasibility

Drop-out is one of the biggest challenges in treatment, and it is often an important explanation for non-optimal effectiveness [69]. The drop-out rates in obese youth during MOT are rather high, sometimes around 27% in hospital-based clinics [70]. It is therefore important to prevent attrition at an early stage, by increasing motivation to complete the training. In this study, we will add several motivational components that are assumed to enhance participation because of their high rewarding value: providing insight in the rationale of the training with attractive materials (such as a “Brain Fitness Guide”) for both children and their parents, giving a scoring schedule that allows participants to save up for a reward, guaranteeing variation in the training sessions (by combining two tasks (attention and inhibition) and by administering different stimuli sets), the use of personalized e-mail reminders, and the use of limited game elements by animated compliments after each session. Furthermore, we will also evaluate the feasibility of the training with participants, their parents and the MOT care providers. Those insights will be supplemented with the drop-out rates and cost and time efficiency analyses. Both insights on motivational encouragement and feasibility analysis could generate a better understanding of drop-out and lead to more satisfaction for users and better adherence rates [71].

### Aims & hypotheses

This RCT mainly aims to test if the computerized program – with 6 weeks intensive and 8 weeks booster training, with a total of 20 training sessions of self-regulation training focusing on inhibition and attention on top of MOT – helps obese children lose weight and maintaining weight loss. We expect that the experimental group will have lost more weight in comparison to the active control group.

To gain insight in the mechanisms of such treatment effect, we also aim to investigate whether or not the training indeed improves self-control and whether these improvements contribute to weight loss (changes in self-control as proposed mediator of treatment effect). Increased self-control is expected in the experimental group compared to the control group, both on the self-control questionnaires and the inhibition and attention task. Additionally, it is useful to investigate transfer of learning by testing performance in the visual search task [44] which comprises both attention and inhibition.

Next to the effects of the primary outcome “weight” (as indexed by a.05 BMI-SDS decrease), more beneficial effects of the training are expected in the experimental group compared to the control group on secondary outcomes: (a) a decrease in maladaptive eating behavior expressed in lower scores on binge eating (Ch-EDE-Q), external eating (DEBQ) and emotional eating (DEBQ); (b) a decrease in comorbid internalizing behaviors expressed in a lower score on internalizing problems (CBCL, YSR) and in a higher feeling of self-esteem (CBSK and CBSA) and (c) a decrease in the components of the metabolic syndrome, endothelial function and OSA. Furthermore, we will explore the influence of potential moderators of the treatment effect: age, gender, IQ, initial BMI-SDS and presence of OSA.

### Statistical analysis

#### Sample size

Power calculations (G*-power, [72]) showed that at least 200 participants (90 per group with 10% drop-out) are needed to detect an effect size of *f* = .10 [73, 74] on weight as the primary outcome (power of .8 & significance level of.05). In the inpatient center, 100 participants will be recruited, and 50 in both outpatient centers.

#### Analytic plan

All data will be analyzed via the intention-to-treat (ITT) principle [75]. Treatment effects will be tested using multilevel analyses, allowing to handle missing and nested data from the three treatment facilities [76]. An autoregressive type of repeated covariance and independent variables will be set up in a model with “group” (experimental, control) and “time” (T0-T4), all two-sided on a *p*-value of <.05 and with effect sizes of generalized eta squares. Data analyses will be documented in a data management form (i.e. about version tracking, save locations, etc.) for safe storage, secrecy and data security.

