## Methods

### Study design and randomization

The effectivity of a computerized “Brain Fitness” EF-training program will be investigated in a prospective, multi-centered RCT by comparing an experimental training group to an active control group in three treatment centers: one inpatient facility (*Zeepreventorium vzw*, De Haan, Belgium) and two outpatient centers (*Jan Palfijn Ziekenhuis Ghent, Belgium* and *Universitair Ziekenhuis Antwerpen*, Belgium). Full information on these participating centers is listed in the Clinical Trials Register with ISRCTN 14722584. The study will be blinded to both participants and treatment center staff (including therapists and laboratory personnel).

Assessment will be done at **five** time points: (1) at admission of the MOT – Multidisciplinary Obesity Treatment (**T0**, pre-treatment), (2) 6 weeks before the end of the intensive period of MOT (approximately 4–10 months after start of treatment) (**T1**, pre EF-training), (3) at the end of the intensive phase of both the MOT and the EF-training on top of the ongoing MOT (**T2**, post EF-training), (4) the end of the booster EF-training with post-treatment personalized contacts in the MOT (**T3**) and (5) a 6-month follow-up after the end of the intensive MOT phase (**T4,** follow-up). For an overview, we refer to the SPIRIT schedule (Table 1; [39]).

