#### Inpatient treatment at the Zeepreventorium VZW

This treatment consists of a 10-month evidence-based MOT [67] for severely obese children and adolescents. A healthy body weight is the primary aim, throughout teaching healthy food behavior and daily physical activity, using various multidisciplinary interventions such as Cognitive Behavioral Techniques (CBT). The parents are involved at a frequent base.

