#### Outpatient treatment at the Jan Palfijn Hospital

An evidence-based program focuses on three components within behavioral lifestyle: healthy eating habits, moderate exercise and Cognitive Behavioral Therapy. A multidisciplinary team, also supervised by a pediatrician, monitors the patient every 2 weeks for an intensive phase of 12 weeks. The standardized outpatient MOT protocol is evidence based, and described in detail in Braet & Van Winckel [7]. The parents are involved at a frequent base.

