#### Intervention: EF-training (“brain fitness”)

In addition to the MOT, each participant will also receive a computerized EF-training in two stages. First, they will train EF abilities during the MOT-intensive phase; containing 12 sessions of approximately 30 min, twice a week for 6 weeks. Second, there is a booster phase directly after completion of the intensive MOT phase, with 8 sessions during 8 weeks (once every week). This training is web-based, so this can be executed in the treatment facility as well as at home. This web-based format allows to track the evolution of each participant, and to send them an invitation each time they have to train.

The experimental as well as the control (sham) training consists of two food-specific tasks targeting inhibition and attention:

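### An autoregressive covariance is fixed for markedly unequal visit intervals; if lag is counted in visits, standard errors are misstated, mostly too large for contrasts from T1

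*Protocol article*

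**What the plan says.** The Analytic plan commits to a model class and a covariance type. The model is multilevel: "Treatment effects will be tested using multilevel analyses, allowing to handle missing and nested data from the three treatment facilities". The covariance is autoregressive: "An autoregressive type of repeated covariance and independent variables will be set up in a model", where the model terms are group and the labelled visits T0 to T4. The plan does not give the order of the autoregression, say whether lag is visit number or elapsed time, or mention a participant random effect.

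The visit timing is spread over several sections:

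- Study design and randomization places T1 at "6 weeks before the end of the intensive period of MOT (approximately 4–10 months after start of treatment") and T4 at "a 6-month follow-up after the end of the intensive MOT phase".
- The inpatient section says: "This treatment consists of a 10-month evidence-based MOT".
- The Jan Palfijn section says the team "monitors the patient every 2 weeks for an intensive phase of 12 weeks". The Antwerp section also gives a 12-week intensive phase, within a programme of 12 to 24 weeks.
- The EF-training section describes an intensive stage "containing 12 sessions of approximately 30 min, twice a week for 6 weeks" and a booster stage "with 8 sessions during 8 weeks (once every week").
- The footnotes to Table 1 restrict outpatient psychological and medical measures to T0, T2 and T4.

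**The concern.** A first-order autoregressive structure indexed by visit uses one correlation per step and lets it decay geometrically with the number of steps. That suits evenly spaced visits. Here one step may be 6 weeks or most of a year, and the T0-T1 step itself differs between settings that each supply half of the planned sample. If part of the variation in BMI-SDS is a lasting difference between children, the correlation over several steps will also stay higher than geometric decay allows.

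The stake is the precision claimed for the group-by-time contrasts. T1 is the pre-training visit, so contrasts from T1 isolate the training effect. The trial is sized at 80% power for a small effect (f = .10) and has little precision to give away. The covariance type is a choice the article makes, not a detail it leaves open.

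**Working it through.** The plan gives no correlation and no standard error, so it has no figure of its own to reproduce on this point. The check has four steps.

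**1. Visit spacing** (one month = 4.35 weeks)

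- T0-T1 inpatient: 10 × 4.35 − 6 = about 37 weeks (8.6 months).
- T0-T1 outpatient, 12-week phase: 12 − 6 = 6 weeks.
- T1-T2: 6 weeks. T2-T3: 8 weeks.
- T3-T4: 6 × 4.35 − 8 = about 18 weeks.

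Inpatient steps therefore differ about six-fold (37/6), and so does T0-T1 between settings. The derived 6-week outpatient gap does not agree with the stated 4 to 10 months, so those passages need reconciling. On the stated range alone, T0-T1 varies 2.5-fold (10/4) and is still far longer than 6 weeks.

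**2. Assumed true covariance**

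The inputs below are assumptions, not figures from the documents:

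- a stable between-child share of 30-85% of the variance;
- a serial part decaying as exp(−gap/30 weeks);
- 2-5% noise;
- half the sample inpatient;
- all five visits at weeks 0, 37, 43, 51, 69 (inpatient) and 0, 6, 12, 20, 38 (outpatient).

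The SD cancels in the ratios below.

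**3. Fit**

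A visit-lag AR(1) covariance V was fitted by population likelihood to the average true covariance S. For each contrast c the ratio is r = √(c′Vc / c′Sc), the model standard error over the true one, with complete data and separate means per group and visit.

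| Contrast | AR(1) only | AR(1) plus participant random intercept |
|---|---|---|
| T2-T1 | 1.10-1.30 | 1.11-1.30 |
| T3-T1 | 1.25-1.35 | 1.11-1.21 |
| T4-T1 | 1.10-1.41 | 0.99-1.03 |
| T1-T0 | 0.87-0.94 | about 0.87-0.94 |

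**4. Consequence for T4-T1 without a random intercept**

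The test rejects when the estimate divided by its true standard error exceeds 1.96r.

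- Type I error = 2[1 − Φ(1.96r)]. For r = 1.102: 2[1 − Φ(2.160)] = 3.1%. For r = 1.406: 2[1 − Φ(2.756)] = 0.6%.
- Power when the true figure is 80% = Φ(2.80 − 1.96r). For r = 1.102: Φ(0.640) = .74. For r = 1.406: Φ(0.044) = .52.

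**Second truth, to test direction.** Take a purely time-based autoregression with correlation 0.90 to 0.99 per month on the inpatient schedule, and fit visit-lag AR(1) to it. The ratios are 1.53-1.68 for T1-T2, 1.36-1.55 for T1-T3 and 1.12-1.25 for T1-T4. They are 0.69-0.73 for T0-T1 and 0.98-1.00 for T0-T4. The sign pattern is the same: too wide from T1, too narrow for T0-T1, and close to correct for T0-T4 under this truth.

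**The case against.** The strongest reply is that the defect is partly inferred. The wording names no order and no lag metric, and a continuous-time structure is also autoregressive. A reader might conclude that the plan treats all steps as equal and that its standard errors will be wrong. The document does not go that far: the misstatement follows only if lag is visit number. That is the natural reading of a repeated covariance over labelled visits, but it is not stated.

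Second, a multilevel model often carries a participant random intercept, which the plan neither states nor excludes. With one, T4-T1 is about right, so the 52-74% power range belongs only to the model without it. The two training-phase contrasts are not rescued.

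Third, no primary contrast is named. A reader might infer either a general loss of power or a general excess of false positives. Neither is supported: contrasts from T1 err conservatively, T0-T1 errs the other way, and T0-T4 depends on the true covariance (0.98-1.00 under the time-based truth, 1.09-1.49 under the mixed one without a random intercept).

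Fourth, the correlations are assumed, and so is a five-visit outpatient schedule. Table 1 is not legible in the text at hand, so the outpatient weight visits cannot be confirmed.

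These points limit the size and certainty of the finding. They do not alter that an autoregressive structure is fixed for unequal visits without tying lag to elapsed time. The unseen analysis plan may clarify the lag, but the choice itself is in the article.

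**Conclusion.** The point holds in conditional form, at moderate severity. The chosen covariance suits the visit schedule badly. If lag is counted in visits and model-based standard errors are used, those for contrasts from T1 are about 10-41% too large without a participant random intercept. With one, T2-T1 and T3-T1 are still about 11-30% too large, and T0-T1 is about 6-13% too small. These sizes rest on the assumed stable share, serial range, noise and visit weeks; the document supplies no correlations. The main consequence is lost power for the training contrasts rather than false positives. With complete data and separate means per visit the effect estimates themselves are unaffected, so this does not amount to a biased treatment effect.

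**What to change.** In the Analytic plan, replace the autoregressive structure with an unstructured covariance across the visits actually measured for each outcome, with Kenward-Roger degrees of freedom. Five visits need 5 × 6 / 2 = 15 covariance parameters, which about 200 children can support. Outpatient psychological and medical outcomes contribute T0, T2 and T4 only. State a fallback in case the model does not converge: a participant random intercept plus a continuous-time (spatial-power) structure on actual assessment dates. If a continuous-time structure was intended all along, the same sentence can say so.

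Reconcile the stated timing of T1 with the programme lengths given for the three centres.

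The cost is about one sentence in the plan, a few more covariance parameters, and a convergence rule fixed before analysis. The fallback also needs assessment dates to be recorded.

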**Table 1 Tab1:**
[figure not shown]
SPIRIT schedule for the WELCOME RCT

^a^Psychological Parameters are: self-control, eating behavior, anxiety, depression, self-esteem

^b^Medical Parameters are blood sampling for metabolic syndromes (kidney function, liver function, insulin/glucose, hormonal status, cortisol, extra serum), peripheral microvascular endothelial function, tonsillar hypertrophy, sleep

^c^In outpatient centers, both medical and psychological parameters are measured only on time points T0, T2 and T4. In the inpatient center, the psychological parameters are also measured on time points T1 and T3

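### T0 is listed as a level of time with no stated baseline adjustment, although it is the only pre-training value for all medical outcomes and for outpatient psychological outcomes; if the effect is the contrast from T0, precision is lost

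*Protocol article*

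**What the plan says.** The Analytic plan section gives one model for all outcomes: "Treatment effects will be tested using multilevel analyses, allowing to handle missing and nested data from the three treatment facilities". It continues with "An autoregressive type of repeated covariance" and states that "independent variables will be set up in a model with “group” (experimental, control) and “time” (T0-T4". Tests are "all two-sided on a *p*-value of <.05". The section names no baseline covariate, no constraint on the T0 means, no group-by-time interaction and no contrast that carries the treatment effect. In Aims & hypotheses, initial BMI-SDS appears only as a moderator to be explored.

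T0 is defined under Study design and randomization as "at admission of the MOT – Multidisciplinary Obesity Treatment (T0, pre-treatment". Footnote c of Table 1 sets the visits: "In outpatient centers, both medical and psychological parameters are measured only on time points T0, T2 and T4", while "In the inpatient center, the psychological parameters are also measured on time points T1 and T3". Inpatients therefore gain T1 and T3 for psychological measures only, and medical outcomes are taken at T0, T2 and T4 in every centre.

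The secondary hypotheses in Aims & hypotheses include "a decrease in the components of the metabolic syndrome, endothelial function and OSA", as well as eating behaviour, internalizing problems and self-esteem.

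**The concern.** In a randomised comparison the two arms have the same expected value at any visit before the training starts. A model with a free mean per arm at T0 ignores this. It estimates a T0 arm difference that is known to be zero in expectation, then subtracts it with all its noise from the later difference. Adjusting for T0 targets the same treatment effect with smaller variance.

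Taking T1 as the baseline is not open for the outcomes named here, because they have no T1 measurement. T0 is at admission. It precedes T2 by the intensive treatment phase, which is 12 weeks in the outpatient programmes and up to about 10 months in the inpatient programme. Weight-loss treatment in between makes a modest correlation plausible, but the document gives no figure for it. At stake is the precision of the secondary comparisons, which the sample size section does not cover.

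**Working it through.** **The plan's own figures.** The document gives no efficiency or power figure for these outcomes. Its sample size concerns weight only: 2 x 90 = 180, and 180/0.9 = 200, so the drop-out step reproduces. It does not bear on the point below.

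**Inputs.**
- Model terms: Analytic plan.
- Visits: Table 1, footnote c.
- 90 per arm after drop-out: Sample size.
- Assumed: the correlation r between T0 and T2, shown over a range, equal variance at both visits (set to 1), and complete data.

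**Reading 1: the effect is the group-by-time contrast of T2 against T0.** With a mean for each arm and visit and complete data, this contrast is the arm difference in mean change from T0, whatever the covariance structure. Per-participant variances are:
- change from T0: 2(1-r)
- adjusted for T0: 1-r² = (1-r)(1+r)
- information lost: 1 - (1-r²)/[2(1-r)] = 1 - (1+r)/2 = (1-r)/2
- extra participants needed to make it up: 2/(1+r) - 1

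| r | change | adjusted | lost at T2 | extra participants | lost at T4* |
|---|---|---|---|---|---|
| .3 | 1.40 | .91 | 35% | 54% | 45.5% |
| .5 | 1.00 | .75 | 25% | 33% | 37.5% |
| .7 | .60 | .51 | 15% | 18% | 25.5% |
| .8 | .40 | .36 | 10% | 11% | 18% |
| .9 | .20 | .19 | 5% | 5% | 9.5% |

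*T4 column: correlation r² between T0 and T4, as under a first-order autoregressive structure with equal steps T0-T2-T4, so the loss is (1-r²)/2. Equal steps are an illustration only.

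A simulation with 90 per arm and 20,000 runs gave T2 losses of 34%, 26% and 15% at r = .3, .5 and .7. When r is below .5, the variance of change, 2(1-r), exceeds 1, so the contrast is less precise than ignoring T0 altogether.

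**In terms of power.** If the adjusted analysis had 80% power, the change analysis would have 62%, 68% and 73% at r = .3, .5 and .7. As a worked case, take a continuous medical outcome measured in all 180 participants, with an assumed standardised difference of .4. The standard error is the square root of (2/90) x variance:
- r = .3: change √(.0222 x 1.40) = .176, power 62%; adjusted √(.0222 x .91) = .142, power 80%.
- r = .5: change √(.0222 x 1.00) = .149, power 77%; adjusted √(.0222 x .75) = .129, power 87%.
- r = .7: change √(.0222 x .60) = .115, power 93%; adjusted √(.0222 x .51) = .106, power 96%.

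**Reading 2: the effect is the group main effect over the visits.** Suppose the arm difference is δ at T2 and at T4. At T0 it is zero in expectation. The simple average over the three visits is (0 + δ + δ)/3 = 2δ/3, so T0 dilutes the effect.

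**The case against.** The strongest reply is that the section does not say what the effect is. It names group and time and lists the visits, but writes out no interaction, contrast or reference visit. That the effect is a change from T0 is therefore an inference. The article is condensed, and a full analysis plan may set covariates or constraints; the listing of T0 to T4 is even compatible with equal arm means at T0. This stands, and it makes the size of the point conditional. It does not remove the point: the model that is stated has T0 as an outcome level with no adjustment, and both natural readings of it are inferior to using T0 as a baseline.

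A reader might infer more than the document supports in four ways:
- **That 15-35% of the information is lost as a fact.** The range is (1-r)/2 for an assumed r of .7 to .3, at T2 only. Elapsed time and intervening treatment make a modest r plausible but do not establish it.
- **That the power figures hold for every outcome named.** They use 90 per arm, the whole trial. The outpatient centres recruit 50 + 50 = 100, so about 100 x 0.9/2 = 45 per arm. If centres are pooled, inpatients contribute T1 and the two-visit formula no longer applies as it stands. The sleep device is used only in children in whom sleep-disordered breathing was found at the first investigation. The categorical definitions of tonsillar hypertrophy and sleep-disordered breathing do not fit a formula for continuous variances.
- **That chance imbalance at T0 is a further harm.** It is the same loss restated, because 2(1-r) - (1-r²) = (1-r)².
- **That the analysis is biased or invalid.** Averaged over randomisation the change estimate is unbiased and type I error is unaffected. A repeated-measures group-by-time analysis is legitimate, and the hypotheses are themselves worded as decreases.

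**Conclusion.** The point holds as a conditional loss of precision on continuous secondary outcomes. The size under the contrast from T0 is (1-r)/2 at T2. It rests on equal variances, complete data and an r that must be assumed: it is substantial if r is .3-.7, small at .8-.9, and larger at T4 if correlation falls with time. Under the main-effect reading the cost is dilution instead. The primary outcome, weight, is outside this point. It is an improvement available at almost no cost, not an error that invalidates the plan.

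**What to change.** State the estimating contrast and how T0 is used.
- **Continuous medical outcomes:** model T2 and T4 with the participant's own T0 value as a covariate, its coefficient allowed to differ by visit. Alternatively, keep T0 as a response and constrain the two arm means to be equal there.
- **Psychological outcomes:** keep the pre-training visits as responses and constrain the arm means to be equal at T0 and, in inpatients, also at T1. Both visits precede the training, so one model serves both visit schedules.
- **Reporting:** give the adjusted arm difference at T2 and at T4.

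The constrained model keeps the handling of missing visits that the plan wants. The change costs wording only, plus a negligible degree of freedom where a covariate is used. It needs no new data, visits or participants.
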